### ParticipatXing institutions

The participating institutions include 31 hospitals in Japan.

## Discussion

This is the first prospective study to evaluate the efficacy and feasibility of durvalumab as maintenance therapy after chemoradiotherapy for patients with unresectable stage III NSCLC who have a PS of 2 and/or are older (i.e., aged > 75 years). In particular, it remains unclear whether durvalumab could display a significant clinical benefit in patients with a PS of 2 after chemoradiotherapy; therefore, the results of our study are expected to elucidate this clinical difficulty. The JCOG0301 study demonstrated that the 5-year survival rate was approximately 15%, which was less than 20%, observed in elderly patients with LA-NSCLC who received daily carboplatin plus concurrent radiotherapy [11]. In future, we expect that the 5-year survival rate will increase to > 20–30% after additional treatment with durvalumab, although our investigation is a phase II study to evaluate the 12-month PFS rate from the initiation of durvalumab. Till date, no prospective study has elucidated the clinical significance of chemoradiotherapy for patients with LA-NSCLC with a PS of 2. Although anti-PD-1/PD-L1 antibodies result in a significant survival benefit for patients with advanced NSCLC with a good PS [18], the efficacy of ICIs is known to increase after radiotherapy [19]; therefore, a synergistic effect is expected for patients with a PS of 2. If mild toxic regimens, such as daily carboplatin—as used in the current study—are combined with concurrent thoracic radiotherapy, the regimen might be feasible for patients with a PS of 2, and sequential therapy with durvalumab will have the potential of improving the survival of such patients. Similarly, ICIs are feasible and effective for elderly patients with NSCLC (aged ≥ 75 years) [18], and we believe that durvalumab as maintenance therapy after chemoradiotherapy is suitable for such patients.

As biomarkers, PD-L1 and the tumor mutation burden are broadly useful for predicting the efficacy of ICIs in patients with advanced NSCLC [19–21]. Recently, we reported that the increased level of CD62LlowCD4 + T cells in the peripheral blood could effectively predict the efficacy and survival of patients with advanced NSCLC who received anti-PD-1 antibodies [22]. It remains unclear whether the value of CD62LlowCD4 + T cells is closely associated with the survival benefit of durvalumab after chemoradiotherapy; however, our exploratory investigation is necessary, as the results will help in the selection of patients who are sensitive to durvalumab.

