**Trial registration:**

During the first registration (before induction chemoradiotherapy), 70 patients will be included; then, we include 58 patients during the second registration (before durvalumab treatment after chemoradiotherapy). https://jcrb.niph.go.jp/.

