## Methods / design

### Study design and objective

The current non-randomized, prospective, open-label phase II study aims to evaluate the efficacy of daily carboplatin plus concurrent thoracic radiation followed by durvalumab for patients with stage III NSCLC who have a PS of 2 and/or are older. The design and protocol of this study are shown in Fig. 1.

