**Fig. 1 Fig1:**
[figure not shown]
Design and protocol of this study

The primary endpoint of this study is the 12-month PFS rate from the initiation of durvalumab. The secondary endpoints are the feasibility, objective response, PFS, OS, and adverse events. As an exploratory analysis, a predictive biomarker for this regimen will be examined using T-cell markers such as CD62LlowCD4 + T cells and CD25 + Foxp3 + CD4+ in the peripheral blood, and considering the expression of PD-L1 within tumor cells and tumor mutation burden before treatment. All procedures will be performed in accordance with the ethical standards of the institutional and/or national research committee and with the 2013 Declaration of Helsinki and its later amendments or comparable ethical standards. Written informed consent is obtained from all participants in our study. This study has been registered in the Japan Registry of Clinical Trials (JRCT) (jRCTs031190070).

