### Statistical analysis

The primary endpoint is to evaluate the progression free survival rate of 12 months from the initiation of durvalumab administration. The secondary endpoint is to investigate the time to failure, the rate of therapeutic completion, progression-free survival, 2-year survival rate, objective response rate, safety and exploratory biomarker assessment. In the PACIFIC study, the 12-month PFS rate was 55.6% after chemoradiotherapy followed by durvalumab and 35.3% after chemoradiotherapy alone. In the JCOG0301 study, the 12-month PFS rate was approximately 30% after radiotherapy with daily carboplatin [11]. According to the retrospective study conducted by Arslan et al. [17], the 1-year OS rate of patients with LA-NSCLC with a PS of 2 was approximately 50%. This was lower than the 1-year OS rate for elderly patients with a good PS (70.8%) observed in the JCOG0301 study. The degree of difference in OS between patients with a poor PS (included in the study by Arslan et al.) and elderly patients (included in the JCOG0301 study) is approximately 30%, which could be applied to the difference in PFS between these populations. Therefore, we assumed that a 12-month PFS rate of 35% after radiotherapy with daily carboplatin followed by durvalumab in eligible patients would indicate potential clinical usefulness, whereas a rate of 20% would be the lower limit for indicating clinical usefulness. On the basis of this assumption, our study was designed to have a power of 80% and had an alpha level of 0.1 (two-sided). The target number of patients for this study is 53. Therefore, we assess 58 patients considering the progressive disease (PD) rate after treatment with radiation with daily carboplatin and patients who dropped out. In the JCOG0301 study, the PD rate was 8%, the rate of treatment-related death was 3%, and the rate of Grade 3–4 adverse events was 6%, so we assumed the dropout rate to be 20%. During the first registration, 70 patients will be included; then, we analyze 58 patients included during the second registration. A minimum follow-up of 12 months is needed after the last patient starts treatment with durvalumab.

Safety evaluation:

We are also investigating the safety in the first 6 patients with a PS of 2.

Further enrollment of patients with a PS of 2 will be stopped until the safety is confirmed in these 6 patients according to the following criteria (Fig. 2):

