## Conclusion

The results of the NEJ039A study will exhibit the efficacy and tolerability of durvalumab as maintenance therapy after daily carboplatin plus radiotherapy, which is among the potential promising first-line treatment regimens for patients who have a PS of 2 and/or are older (aged > 75 years). Moreover, the results of our exploratory investigation are expected to confirm whether the combined assessment of T-cell markers, PD-L1 expression, and tumor mutation burden could predict the outcomes of this regimen.

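### With every analysed patient on durvalumab, the biomarker work can show association with outcome but cannot identify patients sensitive to durvalumab

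*Protocol article*

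**What the plan says.** The Study design and objective section opens with "The current non-randomized, prospective, open-label phase II study" and describes one sequence for everyone: daily carboplatin with thoracic radiotherapy, then durvalumab. The abstract's Trial registration paragraph says "then, we include 58 patients during the second registration (before durvalumab treatment after chemoradiotherapy"), and Statistical analysis says "then, we analyze 58 patients included during the second registration". The primary endpoint is timed from the start of durvalumab. No concurrent or historical group without durvalumab and with marker data is described.

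On the markers (CD62Llow CD4+ T cells, CD25+ Foxp3+ CD4+ cells, PD-L1 expression and tumour mutation burden) the article uses wording of different strength:

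- Study design and objective, text after Fig. 1: "a predictive biomarker for this regimen will be examined using T-cell markers", introduced as an exploratory analysis.
- Discussion: it is unclear whether the T-cell marker is linked to durvalumab's survival benefit, but "the results will help in the selection of patients who are sensitive to durvalumab".
- Abstract (Exploratory assessment) and Conclusion: the question is whether the combined markers predict outcomes of the regimen.
- Statistical analysis: the list of secondary endpoints ends with "objective response rate, safety and exploratory biomarker assessment".

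**The concern.** A prognostic marker separates patients who do well from those who do badly whatever the treatment. A predictive marker separates patients in whom the drug's effect differs. Selecting patients who are sensitive to durvalumab is a claim of the second kind and needs outcomes with and without durvalumab at each marker level. This design supplies only the outcomes with durvalumab.

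The population makes the distinction matter. The trial deliberately mixes PS 2 patients with fit elderly patients, and the article itself expects these groups to differ in outcome. A marker that partly tracks fitness, tumour burden or response to chemoradiotherapy could be associated with PFS without any difference in durvalumab effect. If the Discussion's wording were carried into the report, such an association could be presented as a basis for choosing who should receive durvalumab.

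**Working it through.** **The plan's own figures.** No sample size or power is given for the biomarker work. The only calculation is for the primary endpoint: 20% versus 35%, two-sided alpha 0.1, power 80%, target 53. The arcsine formula ((1.645 + 0.842) / (2(asin √0.35 − asin √0.20)))² gives 53.9, within one patient of the target. Nothing below depends on it.

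**What the design identifies.** For marker group g (+ or −), let λ_g be the hazard of progression or death without durvalumab and θ_g the durvalumab hazard ratio. When everyone is treated, only the products λ_g·θ_g are observed, so the observed marker hazard ratio is

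(λ₊/λ₋) × (θ₊/θ₋).

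The first factor is prognostic and the second is predictive. One observed ratio cannot separate them. The 70 − 58 = 12 patients not expected to reach second registration do not help: the article attributes this loss to progression, toxicity and dropout, so they are not a comparator.

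**Illustration.** Inputs: overall 12-month PFS 35% (Statistical analysis) and durvalumab hazard ratio 0.52 (Background, PACIFIC). Assumed: half the patients marker-positive, observed marker hazard ratio 0.5. With x the 12-month PFS in marker-positive patients, the marker-negative rate is x², so 0.5x + 0.5x² = 0.35 and x = (−1 + √3.8)/2 = 0.475, x² = 0.225. The trial would show about 47% versus 23%. These three situations all produce that split:

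| Situation | Untreated 12-month PFS, marker + | Untreated 12-month PFS, marker − |
|---|---|---|
| Prognostic only, durvalumab without effect | 47% | 23% |
| Prognostic only, durvalumab HR 0.52 in both groups | 0.475^(1/0.52) = 24% | 0.225^(1/0.52) = 6% |
| Predictive only, durvalumab HR 0.5 in marker +, 1 in marker − | 0.475^(1/0.5) = 23% | 23% |

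Only the third would justify selecting patients, and the trial's data cannot tell it from the other two. Over assumed marker hazard ratios of 0.4 to 0.7 and prevalences of 30 to 50%, the observed gap runs from about 32 down to 13 percentage points with no interaction at all.

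**How readily such an association would be found.** Assumed: 58 patients, median split, exponential PFS, follow-up uniform over 12 to 30 months (12 is the article's minimum, 30 is assumed), no durvalumab effect, prognostic hazard ratio 2.0. Simulation (20,000 trials per setting) gives log-rank p<0.05 in about 66% of trials when overall 12-month PFS is 35% (about 47 events on average) and about 70% when it is 20% (about 53 events). The events formula Φ(√d/2 · ln 2 − 1.96) agrees: 66% for d = 47 and 71% for d = 53. Counting only events in the first 12 months at 35% PFS, d = 58 × 0.65 ≈ 38 and the power is 57%.

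**Is a hazard ratio of 2.0 far-fetched?** Statistical analysis quotes 1-year OS of about 50% in PS 2 patients and 70.8% in fit elderly patients. Under exponential survival the ratio is ln 0.50 / ln 0.708 = 2.0, and the article carries the difference over to PFS. A factor of that size is thus already in the planning. How closely the proposed markers follow PS is not stated.

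**The case against.** Most of the marker wording is milder than the Discussion clause. The abstract and the Conclusion ask only whether markers predict outcomes of the regimen, which a single arm can address as prognosis under treatment. The design section's term can be read as loose usage for the same thing. The Discussion sentence also begins by admitting uncertainty and calls the work exploratory. No marker result governs eligibility, treatment or any decision rule. All of this stands and limits the weight of the point. It does not rescue the selection claim: an exploratory label lowers the certainty of a result but does not turn an association under treatment into evidence of treatment sensitivity.

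A reader might infer more than the article supports:

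- *That the Conclusion promises confirmation of a signature.* It says "the results of our exploratory investigation are expected to confirm whether the combined assessment of T-cell markers" and the other markers could predict outcomes of the regimen. The word whether leaves the answer open, and the target is outcome, not durvalumab effect.
- *That the status of the work is contradictory.* Statistical analysis places it in the secondary list but still names it exploratory. Its placement is editorial.
- *That chance findings from searching for cut-offs are built in.* The article describes no cut-off rule or data-driven search, and such rules commonly sit in the full protocol or SAP, which are not shown.
- *That frail patients will be treated or refused on a marker.* No written step leads there.

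**Conclusion.** The concern holds in a limited form. Two places, the predictive-biomarker aim in Study design and objective and the durvalumab-selection claim in the Discussion, describe a property that this design cannot establish. That rests on the design alone: one treatment sequence, 58 analysed patients all registered for durvalumab, no comparator with marker data. The 65 to 70% figure rests on the assumed hazard ratio of 2.0, median split, exponential PFS and follow-up. It shows only that a purely prognostic marker could well reach significance here, and it should not be read as a false-positive rate of the plan. Severity is minor: the primary endpoint, sample size and safety rules are unaffected, and what changes is the conclusion that the biomarker analysis may support.

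**What to change.** In Study design and objective, replace the predictive-biomarker aim with the association of the named markers with outcome after this regimen, described as hypothesis-generating. In the Discussion, delete the claim about selecting patients sensitive to durvalumab, and add that separating predictive from prognostic value would need a comparator without durvalumab and with the same marker data. Optionally, as an editorial matter, list the biomarker item apart from the secondary endpoints in Statistical analysis.

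The article is already published, so the practical place for the change is the full protocol, the SAP if there is one, and the results report. The cost is a few sentences and a more modest claim. No patients, samples or assays are added.

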## Conclusion

The results of the NEJ039A study will exhibit the efficacy and tolerability of durvalumab as maintenance therapy after daily carboplatin plus radiotherapy, which is among the potential promising first-line treatment regimens for patients who have a PS of 2 and/or are older (aged > 75 years). Moreover, the results of our exploratory investigation are expected to confirm whether the combined assessment of T-cell markers, PD-L1 expression, and tumor mutation burden could predict the outcomes of this regimen.

## Data Availability

Not applicable.

## Abbreviations

LA-NSCLC: Locally advanced non-small cell lung cancer
PS: Performance status
PFS: Progression-free survival
NSCLC: Non-small cell lung cancer
HMGB-1: Overall survival: OS; high-mobility group protein box-1
PD-L1: Programmed death receptor 1-ligand
PD-1: Programmed death 1
JRCT: Japan Registry of Clinical Trials
PET: Positron emission tomography
CT: Computed tomography
DLTs: Dose limiting toxicities
